# Corindus Randomised Controlled Trial Summary

| **Title:** | Percutaneous Coronary Intervention using assisted robotic technology: a randomised controlled trial |
| --- | --- |
|  |  |
| **Short Title:** | **P**CI using **A**ssisted **R**obotic **T**echnolog**Y** trial: the **PARTY** trial |
|  |  |
| **Study Description:** | Coronary artery disease is a leading cause of death globally, nationally and locally. Currently in South Western Sydney Local Health District Interventional Cardiologists perform Percutaneous Coronary intervention (PCI) procedure which opens coronary arteries that are narrowed or blocked by the build-up of atherosclerotic plaque. PCI may also be used to relieve symptoms of coronary heart disease or to reduce heart damage during or after a heart attack.  With new technology, engineering and training development, a technology-assisted percutaneous coronary intervention (PCI) device has the potential to increase procedural accuracy, reduce radiation exposure to participants and staff, improved ergonomics, and reduce major adverse cardiac events. To date we are not aware of any randomised controlled trial data supporting this technology |
| **Study Design:** | This is a randomized controlled trial of the CorPath GRX System versus standard PCI to compare participant outcomes at 72 hours post-procedure or hospital discharge, day 30 and 1 year. |
|  |  |
| **Study Objective:** | This study will assess the safety, effectiveness including the clinical and technical performance and cost analysis of technology-assisted PCI versus standard PCI performed by a cardiologist in a randomised controlled trial. |
| **Effectiveness Performance Measures:** | **Clinical Success:**  Less than 30% residual stenosis (visual estimate) post PCI, without in-hospital major adverse coronary events (MACE).  **Technical Success:**  Defined as successful completion of the PCI absent ***unplanned*** conversion to manual operation of guidewires or balloon/stent catheter or inability to navigate vessel anatomy or poor guide catheter support. |
|  |  |
| **Safety Measures:** | **Major Adverse Cardiac Event (MACE):**  MACE that occurs within 72 hours of the procedure or prior to hospital discharge, whichever occurs first, day 30 and 1 year  **Serious Adverse Events:**  All Serious Adverse Events (SAEs) from the start of the PCI procedure until the end of the study will be summarized. |
| **Cost Measures:** | Total procedural cost of PCI at day 30 and 1 year |

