### 1.3.1 Potential Risks

Participants may be exposed to potential risks from participating in this study. Potential procedure and device related adverse events that may occur and/or require intervention are described below. The primary risks of the procedure are believed to be similar to the risks of participants undergoing procedures requiring PCI. Complications may occur at any time during the procedure. Potential risks of the PCI are:

- Injury to the hearts arteries including tearing and rupture
- Infection, bleeding and bruising at the catheter site
- Allergic reaction or kidney damage due to the dye or contrast used
- Blood clots that can lead to stroke or heart attack
- Bleeding into the abdomen

This study involves exposure to a small amount of radiation during the coronary angiogram which the participant would be receiving as standard care. Radiation may slightly elevate the risk for cancer. There is no increase in risk of exposure as a result of participating in this study.

Complications may occur at any time during the procedure. The study may involve unknown or unforeseen side effects or complications other than those mentioned above.

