### Serious Adverse Events

All Serious Adverse Events (SAEs) from the start of procedure until the end of the study will be summarized.

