## **Schedule of Events**

| **Exam/ Test/ Data Collection** | **Screening** | **Index**  **Procedure** | **Day 3/ discharge** | **Day 30**  **(±5 days)** | **EOS / Day 365**  **(±14 days)** |
| --- | --- | --- | --- | --- | --- |
| Informed consent | X | X |  |  |  |
| Medical history | X |  |  |  |  |
| Demographics | X |  |  |  |  |
| Vital signs including height, weight^1^ | X | X^6^ | X^6^ |  |  |
| Physical examination | X^1^ |  | X |  |  |
| 12 lead ECG | X^4^ |  | X |  |  |
| non-cardiac laboratory assessments | X |  | X |  |  |
| Cardiac enzymes | X^2^ |  | X^3^ |  |  |
| Inclusion/ exclusion criteria | X |  |  |  |  |
| Randomisation |  | X |  |  |  |
| PCI |  | X |  |  |  |
| Dosimeter reading |  | X |  |  |  |
| Fluoroscopy reading |  | X |  |  |  |
| Lesion assessment |  | x |  |  |  |
| Time of procedure |  | X |  |  |  |
| Contrast usage |  | X |  |  |  |
| Equipment usage |  | X |  |  |  |
| Concomitant medications | X | X | X | X | X |
| Adverse Events^5^ |  | X |  |  |  |
| Health care resource usage |  | X | X | X | X |
| Event Assessment |  | X | X^5^ | X^5^ | X^5^ |
| Complete Case Report Form | X | X | X | X | X |

^1^ Within 30 days of index procedure

^2^ Pre-procedure cardiac enzymes within 7 days of index procedure, if collected.

^3^ Post-procedure cardiac enzyme collection is left to the discretion of the investigator and shall be dictated by the participant’s clinical symptoms.

^4^ Post-procedure 12-lead ECG: it is recommended that an ECG be performed at the time of discharge but is not required for the protocol.

^5^ Related to procedure, intervention or Adverse Event of Special Interest (MACE)

^6^ height and weight only required at screening

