### Event Assessments

This study is not using any unregistered products therefore only serious adverse events that meet the MACE definition will be reported from visit 2 until the end of study visit (visit 5). Event Assessments will be reviewed by the End-Point Adjudication Committee.

**Major Adverse Cardiac Event (MACE):** MACE is defined as cardiac death, Q-wave or non Q-wave myocardial infarction (MI), or clinically driven target vessel revascularization (TVR) by percutaneous or surgical methods.

**Cardiac Death:** Death due to cardiac causes. If the cause of death cannot be determined, it will be categorized as cardiac.

Myocardial Infarction (Protocol Definition):

Clinically relevant MI after coronary revascularization will be defined by the 4^th^ Universal Definition of PCI related MI. Events as defined by the Society for Cardiovascular Angiography and Interventions definition for periprocedural MI will also be recorded.

The 4th Universal Definition of PCI related MI defines:

- Participants with normal baseline cardiac biomarkers
  - Cardiac troponin (cTN) >5x the 99^th^ percentile of upper reference limit (URL)
- Participants with elevated baseline cardiac biomarkers
  - Rise in post procedure cTN by >20% and be at least >5x 99^th^ percentile of URL AND
  - At least one of the following
    - New ischaemic ECG changes
    - Development of new pathological Q waves
    - Imaging evidence of new loss of viable myocardium or new regional wall motion abnormality in a pattern consistent with an ischaemic aetiology
    - Angiographic findings consistent with a procedural flow limiting complication such as coronary dissection, occlusion of a major epicardial artery or a side branch occlusion/thrombus, disruption or collateral flow or distal embolisation

The Society for Cardiovascular Angiography and Interventions definition for periprocedural MI defines:

- Participants with normal baseline cardiac biomarkers
  - CK-MB >10x upper limit normal (ULN) or cTn (I or T) >70x ULN, or
  - CK-MB >5x ULN or cTn >35x ULN plus new Q-waves in >2 contiguous leads or LBBB
- Participants with elevated baseline cardiac biomarkers
  - Baseline biomarkers are stable or falling:
    - CK-MB >10x ULN or cTn (I or T) >70x ULN of **most recent pre-procedure level**, or
    - CK-MB >5x ULN or cTn >35x ULN of **most recent pre-procedure level** plus new Q-waves in >2 contiguous leads or LBBB

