### Reporting Requirements of SADEs

This study does not require serious adverse event reporting as all products used are being used within indication of the listing on the Australia Registry of Therapeutic Goods (ARTG). However in accordance with TGA requirements an automatic condition of inclusion under 5.7 of the [Therapeutic Goods (Medical Devices) Regulations 2002](https://www.legislation.gov.au/Series/F2002B00237) sponsors of a medical device report adverse events or near adverse events to the TGA [Incident Reporting and Investigation Scheme (IRIS)](https://www.tga.gov.au/node/289286).

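### The safety measure is all SAEs to end of study, but the event rules give no clear collection route for an SAE that is neither MACE nor judged related

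*Protocol*

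**What the plan says.** The safety measure is stated twice. The Summary, under Safety Measures, has "All Serious Adverse Events (SAEs) from the start of the PCI procedure until the end of the study will be summarized". Section 2.4.2 has "All Serious Adverse Events (SAEs) from the start of procedure until the end of the study will be summarized". In both places MACE is listed as a separate safety measure. Appendix A defines seriousness by the usual general criteria and counts an adverse event whether or not it is thought to be device related.

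The rules that supply the data are narrower:

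- Section 7.7.2: "only serious adverse events that meet the MACE definition will be reported from visit 2 until the end of study visit" (visit 5). The same section says that "MACE is defined as cardiac death, Q-wave or non Q-wave myocardial infarction (MI), or clinically driven target vessel revascularization (TVR) by percutaneous or surgical methods".
- Section 7.7.1: staff watch for adverse events related to the device or the procedure. Those events are followed to day 30, to resolution, or until judged stable.
- Section 3.3, footnote 5, which marks the Adverse Events row and the post-procedure Event Assessment cells: "Related to procedure, intervention or Adverse Event of Special Interest (MACE").
- Section 7.8.2: "This study does not require serious adverse event reporting". The reason given is that all products are used within their registered indication.

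The Schedule marks the Adverse Events row at the index procedure only. Sections 7.3, 7.5 and 7.6 each list an adverse event assessment at the later visits.

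**The concern.** Safety is part of the primary objective (Section 2.1), and the all-SAE summary is one of the two safety measures. A site following Sections 7.7.1 and 7.7.2 would not necessarily enter every event that the measure is said to contain, and an analysis plan cannot recover events that were never recorded.

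The omission also need not be the same in the two arms. Outside MACE, whether an SAE is captured depends on the investigator calling it related (Section 7.7.4). Section 8.1 describes the trial as open-label, and the investigator is told the allocation (Section 5.3). The device-related category applies to use of the study device, so it has no natural counterpart in a participant treated manually throughout. A difference between arms in non-MACE SAEs could then reflect attribution as well as harm.

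**Working it through.** The protocol states no figure on this point, so the check is to follow each kind of SAE through the rules.

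**Step 1: is the promised measure wider than MACE?** Yes. MACE and SAEs are listed as two measures, and the Appendix A definition of seriousness goes well beyond cardiac death, MI and TVR.

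**Step 2: which route does each SAE have after the procedure?**

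| SAE | Within MACE (7.7.2)? | Within the related-event rule (7.7.1, footnote 5)? | Clear route to visit 5? |
| --- | --- | --- | --- |
| Cardiac death, or death of undetermined cause (counted as cardiac) | Yes | Not needed | Yes |
| MI or clinically driven TVR, as defined | Yes | Not needed | Yes |
| Stroke, bleed or renal injury judged related | No | Yes | Yes |
| Stroke, bleed or renal injury judged unrelated | No | No | No |
| Death from a known non-cardiac cause, judged unrelated | No | No | No |
| Other hospitalisation judged unrelated | No | No | No |

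The last three rows are SAEs under Appendix A and so belong in the summary promised by the Summary and Section 2.4.2.

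**Step 3: does another section supply the missing route?**

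- Section 7.2.3 collects any adverse event during the procedure. That covers the procedure itself, not follow-up.
- Section 7.2.8 asks for all adverse events after the procedure, but as set out in Section 7.7, which is the restrictive section.
- Section 7.8.1 requires a separate form for each event. It does not say which events qualify.
- Section 10.1 asks for eCRF documentation of procedural events and device complications, which is again the related set.
- Sections 7.3, 7.5 and 7.6 schedule an assessment at each later visit without widening its scope. Sections 7.3 and 7.5 refer to Section 7.6 for the method, but that is the Day 365 visit; the adverse event rules are in Section 7.7.

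None of these clearly brings in a non-MACE SAE judged unrelated after the procedure.

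**Step 4: does "only serious adverse events that meet the MACE definition will be reported from visit 2 until the end of study visit" concern regulatory reporting only?** The reason given, that no unregistered product is used, points that way. But the sentence is framed by study visits and is followed by review by the adjudication committee. Footnote 5 imposes a similar limit in a table of data collection. On its face the restriction reaches data collection, and nothing in the text confines it to regulatory reporting.

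**The case against.** The strongest opposing case is that the protocol collects a good deal more than MACE, and this stands. A reader might infer that stroke, bleeding and kidney injury are missed outright, since Section 1.3.1 names them as risks of PCI (for example "Blood clots that can lead to stroke or heart attack") and none is in MACE. The documents do not support that. When judged related to the procedure or device, such events fall under Section 7.7.1 and footnote 5, with a form under Section 7.8.1. Renal function is also assayed at Day 3 or discharge.

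Nor does it follow that no SAE summary can be produced. A summary of MACE plus related SAEs is available; what is not assured is completeness. Deaths of undetermined cause count as cardiac, and Section 6.2 has the site check whether a participant who misses a visit is alive, so non-cardiac deaths may come to light even though no rule requires them as SAEs.

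Section 7.8.2 is weak evidence for a collection gap. It sits under device-effect reporting, rests on registration status and turns at once to incident reporting to the regulator. It is best read as regulatory. The unmarked Adverse Events cells look like a clerical mismatch, because the Event Assessment row is marked at every later visit.

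It can also be argued that the unrelated category in Section 7.7.4 implies that unrelated events are entered. That does not settle it: a MACE event can itself be unrelated, so the category has a use under the narrow rule too.

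**Conclusion.** The contradiction holds in a limited form. The stated measure covers all SAEs to end of study; the operative rules cover MACE plus events judged procedure- or device-related. The gap is the non-MACE SAE judged unrelated, mainly after discharge and up to day 365, in both arms. The all-SAE summary cannot be complete as defined, and its non-MACE part depends on an open-label relatedness judgement.

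The size can be given only as a class of events. The documents contain no SAE rate from which to count the participants affected. That capture will differ between arms is a possibility created by the design; the protocol does not show that it will happen. The conclusion assumes that sites apply Sections 7.7.1, 7.7.2 and footnote 5 as written. If the restriction in Section 7.7.2 was meant for regulatory reporting alone, the protocol needs to say so, and footnote 5 would still limit what is collected.

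**What to change.** Reconcile the Summary, Sections 2.4.2, 7.7.1, 7.7.2 and 7.8.2, and footnote 5 of Section 3.3.

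Preferred:

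- Amend Section 7.7.2 and footnote 5 so that every SAE meeting the Appendix A definition, including death from any cause, is recorded in the eCRF in both arms from the start of the procedure to visit 5, regardless of relatedness. Align Section 7.7.1 with this.
- Mark the Schedule's Adverse Events row at Day 3/discharge, Day 30 and Day 365 to agree with Sections 7.3, 7.5 and 7.6, and correct the cross-references in Sections 7.3 and 7.5.
- State that Section 7.8.2 concerns regulatory reporting only.

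The cost is a short amendment and some extra eCRF entry at visits that already take place; regulatory reporting does not change. It is best done before more follow-up accrues, because events not recorded at the time may be only partly recoverable from records.

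Alternative: restate the measure in the Summary and Section 2.4.2 as MACE plus procedure- or device-related SAEs, and acknowledge that its non-MACE part depends on an open-label relatedness judgement. This adds no data entry, but gives up the all-SAE comparison that the protocol now promises.

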### 2.2.1 Clinical Success

Defined as less than 30% residual stenosis (visual estimate) post PCI in the lesion(s) treated, without in-hospital MACE.

MACE is defined as cardiac death, clinically relevant MI after coronary revascularization (Q-wave or non-Q-wave myocardial infarction), or clinically driven target vessel revascularization (TVR) by PCI or CABG. Clinically relevant MI after coronary revascularization will be defined by the 4^th^ Universal Definition of PCI related MI. Events as classified by the Society for Cardiovascular Angiography and Interventions definition for periprocedural MI will also be recorded for additional analysis.

The 4th Universal Definition of PCI related MI defines:

- Participants with normal baseline cardiac biomarkers
  - Cardiac troponin (cTN) >5x the 99^th^ percentile of upper reference limit (URL)
- Participants with elevated baseline cardiac biomarkers
  - Rise in post procedure cTN by >20% and be at least >5x 99^th^ percentile of URL AND
  - At least one of the following
    - New ischaemic ECG changes
    - Development of new pathological Q waves
    - Imaging evidence of new loss of viable myocardium or new regional wall motion abnormality in a pattern consistent with an ischaemic aetiology
    - Angiographic findings consistent with a procedural flow limiting complication such as coronary dissection, occlusion of a major epicardial artery or a side branch occlusion/thrombus, disruption or collateral flow or distal embolisation

The Society for Cardiovascular Angiography and Interventions definition for periprocedural MI defines:

- Participants with normal baseline cardiac biomarkers
  - CK-MB >10x upper limit normal (ULN) or cTn (I or T) >70x ULN, or
  - CK-MB >5x ULN or cTn >35x ULN plus new Q-waves in >2 contiguous leads or LBBB
- Participants with elevated baseline cardiac biomarkers
  - Baseline biomarkers are stable or falling:
    - CK-MB >10x ULN or cTn (I or T) >70x ULN of **most recent pre-procedure level**, or
    - CK-MB >5x ULN or cTn >35x ULN of **most recent pre-procedure level** plus new Q-waves in >2 contiguous leads or LBBB
  - Baseline biomarkers have not been shown to be stable or falling: CK-MB (or cTn) rises by an absolute increment equal to those recommended above plus new ST-segment elevation or depression plus signs consistent with a clinically relevant MI, such as new onset or worsening heart failure or sustained hypotension.

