**Post Procedure Participant Evaluations**

- Clinical assessment and physical examination
- Record of all adverse events as described in Section 7.7
- If clinically indicated as determined by the investigator
  - 12-lead ECG
  - CK, CK-MB and/or Troponin

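### The troponin rule for PCI-related MI asks for supporting evidence of ischaemia only when baseline biomarkers are elevated; at normal baseline, troponin above 5 times the limit is enough on its own

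*Protocol*

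**What the plan says.** Section 2.2.1 (Clinical Success) and section 7.7.2 (Event Assessments) give the same rule in the same layout. Both introduce it this way: "Clinically relevant MI after coronary revascularization will be defined by the 4^th^ Universal Definition of PCI related MI".

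- **Normal baseline biomarkers.** There is a single bullet, "Cardiac troponin (cTN) >5x the 99^th^ percentile of upper reference limit (URL"), and nothing follows it in that branch.
- **Elevated baseline biomarkers.** The branch reads "Rise in post procedure cTN by >20% and be at least >5x 99^th^ percentile of URL AND", followed by "At least one of the following" and four kinds of supporting finding: new ischaemic ECG changes, new pathological Q waves, imaging evidence, or an angiographic flow-limiting complication.

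The MI rule feeds two outcomes. Section 7.7.2 states: "MACE is defined as cardiac death, Q-wave or non Q-wave myocardial infarction (MI), or clinically driven target vessel revascularization (TVR"). Section 2.2.1 gives clinical success as: "Defined as less than 30% residual stenosis (visual estimate) post PCI in the lesion(s) treated, without in-hospital MACE".

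The protocol is not consistent on who has troponin measured after PCI. Footnote 3 to the Schedule of Events says: "Post-procedure cardiac enzyme collection is left to the discretion of the investigator". The post-procedure evaluations in section 7.2.8 carry the condition "If clinically indicated as determined by the investigator". Section 7.3 (Day 3 or Discharge) lists cardiac enzymes among the evaluations to be performed, without that condition.

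**The concern.** Take two participants with the same post-procedure troponin of 6 times the limit, an unchanged ECG, no imaging change and a clean angiogram. One had normal baseline biomarkers; the other had elevated ones and a rise of more than 20%. As written, the first has an MI and a MACE, and the second has neither. Nothing in the protocol explains why the participant with the normal baseline should need less evidence, and an event with no ECG, imaging or angiographic sign is hard to reconcile with a label of clinical relevance.

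MACE is the first-listed safety measure and clinical success the first-listed effectiveness measure. Three things are at stake:

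- Events without supporting evidence of ischaemia can enter both measures.
- Event rates would depend partly on the mix of normal and elevated baselines.
- Under a troponin-only rule the MI count depends on who is tested. Two places leave testing to the investigator, and section 8.1 describes the trial as open-label.

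**Working it through.** **Step 1. Read the rule in both places.** The nesting is identical in sections 2.2.1 and 7.7.2, so one operative section does not correct the other. Appendix A, under its own heading of protocol definition, gives a third text: biomarkers alone suffice only at CK-MB above 10 times or troponin above 70 times the upper limit of normal, with lower thresholds (5 and 35 times) if new Q waves or LBBB are present. It contains no 5-times rule.

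**Step 2. Check the plan's own power figure.** Section 8.1 powers the trial on patient radiation exposure only.

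- Difference: 0.20 × 1284 = 256.8 mGy.
- Standard error: √(180²/150 + 142.83²/150) = 18.76.
- Ratio: 256.8 / 18.76 = 13.7, so power is effectively 100%.

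This agrees with the stated figure of above 99%. No power statement rests on MI, MACE or clinical success, so the MI rule does not touch the sample size.

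**Step 3. Set up the size of the effect.** Inputs from the protocol:

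- 150 participants per arm (section 8.1).
- 97.6% clinical success in a cited robotic study (section 1.3.2), hence 2.4% failure. This figure is per lesion; using it per participant is an approximation. It gives 150 × 0.024 = 3.6 failures per arm.

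Assumptions, with no source in the protocol:

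- L: share of participants with normal baseline and an isolated troponin rise above 5 times the limit.
- q: share of participants sampled after PCI, taken as unrelated to having an isolated rise.

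Added failures per arm = 150 × L × q × (1 − 0.024) = 150 × L × q × 0.976. The last factor leaves out those already counted as failures.

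| L | q = 10% | q = 50% | q = 100% |
| --- | --- | --- | --- |
| 2% | 0.3 (8%) | 1.5 (29%) | 2.9 (45%) |
| 5% | 0.7 (17%) | 3.7 (50%) | 7.3 (67%) |
| 10% | 1.5 (29%) | 7.3 (67%) | 14.6 (80%) |
| 20% | 2.9 (45%) | 14.6 (80%) | 29.3 (89%) |

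In brackets: added failures as a share of all failures, that is added / (added + 3.6).

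**Step 4. Break-even.** Isolated rises make up more than half of failures when L × q × 0.976 > 0.024, that is when L × q > 0.0246, or about 2.5%. With everyone sampled this needs L of about 2.5%; with half sampled, 4.9%; with a quarter, 9.8%; with a tenth, 24.6%.

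**Step 5. With the supporting-evidence list applied to both strata,** isolated rises add no failures, and the count returns to about 3.6 per arm at the cited rate.

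**The case against.** **It may be a layout slip.** The governing sentence names the 4th Universal Definition, the bullets summarise it, and the list may have been indented one level too far. That is possible, and the cited source is not at hand to settle it. But the same nesting stands in both operative sections. Section 10.2 says what material the adjudicators review and gives them no authority to add a criterion. The protocol should not leave them to guess.

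**Symptom-driven sampling would miss most isolated rises.** This stands as a limit on size: an asymptomatic participant is the one whom the Schedule of Events footnote and section 7.2.8 would leave untested. Section 7.3 points the other way, and discretionary testing brings its own risk that the arms are tested differently.

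**Only serious events meeting the MACE definition are reported.** That sentence in section 7.7.2 governs event reporting. It does not alter the definition of MI.

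**A stronger reading is tempting: that isolated rises will swamp the few real events and destroy power.** The documents do not support it. For an assumed 2.4% versus 10% failure, Fisher power with 150 per arm is 73%. It falls to 46%, 31% and 19% if isolated rises affect a further 5%, 10% and 20% of otherwise successful participants in both arms, but only to 70%, 66% and 60% at 0.5%, 1% and 2%. The 10% comparator and the rates are assumptions. The model also adds events to both arms, whereas section 7.7.2 and Appendix A word in-hospital MACE as occurring in a participant treated with the CorPath GRX System. Read literally, the route to clinical failure exists in one arm only.

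**A reader might also infer that the stricter companion definition contradicts the 5-times rule.** Within sections 2.2.1 and 7.7.2 it does not: it is a separate definition, recorded for additional analysis, and offers a partial safeguard. The conflict is with Appendix A, which presents those thresholds as the protocol definition.

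**Conclusion.** The point holds as a defect in a stated endpoint rule. Supporting evidence is required in one baseline stratum and not in the other, without a reason given, and an isolated rise at normal baseline counts as an MI, a MACE and, in hospital, a clinical failure.

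The size is open. Over the values tabulated, the addition runs from 0.3 to about 29 failures per arm against about 3.6, and isolated rises outnumber other failures only if L × q exceeds about 2.5%. This rests on assumed L and q and on a lesion-level failure rate from a cited study. The sample size stands. This should be fixed before events are adjudicated, but it does not threaten the powered comparison.

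**What to change.** 1. In sections 2.2.1 and 7.7.2, move the supporting-evidence list out one level so that it applies to both baseline strata, after checking the wording against the cited 4th Universal Definition.
2. Reconcile Appendix A with those sections, so that one MI definition governs MACE and the other is labelled as additional.
3. Record an isolated troponin above 5 times the limit separately as myocardial injury, outside MACE and clinical success.
4. Reconcile the Schedule of Events footnote, section 7.2.8 and section 7.3 on post-procedure troponin, so that ascertainment is the same in both arms.

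The cost is a wording change and matching instructions to the adjudicators. ECGs and angiograms are already among the source data listed in section 10.2. The downside is small: fewer events will count as MACE.
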